**8.15 Study visit 15 – Follow up**  
**(Study week 48; 14 days after V14 +/- 3 days)**

This is the first follow up visit two weeks post 2nd MVA/Placebo vaccination. It is essentially a safety assessment visit and will be conducted as described for study visit 4. Blood draw (including Troponin I test when available) and filling of forms will be done according to the visit schedule. In addition a post vaccination ECG will be performed and results will be interpreted and compared to previous ECG as described for Study Visit 12. The participant will then be compensated and assigned to his next scheduled visit.

**8.16 Study visit 16 – Follow up**  
**(Study week 50; 28 days after V14 +/- 5 days)**

This is the second follow up visit post 2nd MVA/Placebo vaccination. It is essentially a safety assessment visit and will be conducted as described for study visit 7. Blood draw and filling

of forms will be done according to the visit schedule. The participant will then be compensated and assigned to his next scheduled visit.

#### **8.17 Study visit 17 – Follow up (Study week 58; 84 days post V14 +/- 14 days)**

This is the first long time follow-up visit after the completed vaccination schedule. It is essentially a safety and immunogenicity assessment visit. It will be conducted by the study nurse(s) and the study doctor. A risk assessment and risk behavior counseling as well as pre HIV test counseling will be performed. Vital signs will be recorded, blood will be drawn according to the flow chart and participants will be seen by the medical officer for medical status recording. CRF's are filled according to flow chart. The participant will then be compensated and assigned to his next scheduled visit.

Post HIV test counseling will be performed 2-3 weeks after this visit only by the nursing/counseling staff in the case of negative test results. This post HIV test contact will be recorded as an additional study visit (Visit 17J) and compensated as indicated for unscheduled visits.

#### **8.18 Study visit 18 – Final study visit (Study week 70; 168 days post V14 +/- 14 days)**

This is the second long time follow up visit after the completed vaccination schedule and the final study visit. It is essentially a safety and immunogenicity assessment visit. The study nurse(s) and the study doctor will conduct it. Pre HIV test counseling and extended risk assessment and risk behavior counseling is performed. Vital signs will be recorded and blood will be drawn according to the flow chart. The medical officer will conduct a medical status examination and forms will be filled according to the visit schedule including the disclosure of the Patients Status Form (**CRF 7-I**), the Concomitant Medication Form (**CRF 4-I**) and the Adverse Events Form (**CRF 6-I**). Ongoing or new medical events if not related to the study agents will be reported and might be followed up in 1 or 2 additional unscheduled visits but should preferentially be referred to the appropriate health facilities for further management. In the case of ongoing pregnancies study visits will proceed as unscheduled visits until pregnancy and infant outcome can be recorded. Volunteers may be asked to participate in long-term follow-up studies. All study volunteers will be issued a card signed by the principal investigators (full names, tel. numbers and addresses) stating that the holder has participated as a volunteer in a HIV-1 immunization study and that the outcome of standard HIV diagnostic tests do not signify HIV-1 infection. Study participants will be invited to perform HIV testing if wished by the study site also after the completion of the study.

Post HIV test counseling will be performed 2-3 weeks after this visit only by the nursing/counseling staff in the case of negative test results. This post HIV test contact will be recorded as an additional study visit (Visit 18J) and compensated as indicated for unscheduled visits.

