### 8.1 Screening I (Study Visit 1, 4-8 weeks before enrolment)

#### 8.1.1 Informed consent procedures and study information

The first screening visit (study visit 1) will take place between 4 and 8 weeks before the first planned injection. At this visit the study volunteer will meet the study doctor(s) and study nurse(s), and the trial will be discussed in detail associated with thorough informed consent procedures (**see Appendix 4 A or B**). This discussion will also address on the following: the meaning of 'randomization', potential adverse effects of the vaccine, and about the fact that it is unknown whether or not the study vaccines will protect or even increase the risk for him/her to acquire HIV infection. They will be informed that following immunization they may develop antibodies that will produce a positive reaction in a routine HIV test, but that provisions have been made to distinguish between a post vaccination response and HIV infection during and after the trial. This includes that volunteer will be excluded from donating blood or organs and that they may be vulnerable to social risk if they develop HIV antibodies, or by revealing their participation in the study. They will be assured of the level of care that will be made available to them should they be found to be HIV infected at any time during their participation in the study, including the screening period (see also section 17.1). HIV infections occurring after the study and observation period will be handled in the regular established HIV clinic in the police force or community as applicable. The placebo concept will also be explained. Study Participants who have received and signed the initial informed consent (Version 2.0, September 2009) will receive written information regarding the changed visit schedule. Signed and dated informed consent will be requested (**see Appendix 4 C and D**).

Volunteers will be counseled by study personnel about safer sex. They will be counseled on the importance of contraception from starting immunization up to 3 months after the last immunization and that they should continue to use condoms with sexual partners whose HIV status is not known. They will also be reminded about these items on each day of immunization. High quality hypoallergenic condoms will be provided free of charge to volunteers throughout the trial.

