### 17.2 HIV testing

Only volunteers with a non-reactive antigen/antibody HIV ELISA result will be enrolled. The HIV testing (simple rapid Antibody test at the Laboratory) will be obtained before each vaccination and at the long-term follow-up visit at study weeks 84 (Visit 18) and 108 and whenever a volunteer has the need to establish his/her HIV status (Visit 19).

It is possible that volunteers may develop antibodies and test 'positive' in routine commercial HIV ELISA assays subsequent to immunization. The laboratories at MUHAS, Department of Microbiology/Immunology and MMRP, will conduct molecular tests (HIV-1 PCR) to distinguish between infection and a post-immunization response required either for clinical management, or at the request of a volunteer. For unblinding reasons laboratories will only provide the

information to the clinic whether a participant is “infected” or “uninfected” to not expose false positive ELISA results suggestive for vaccine or placebo randomization.

After study completion participants will be advised to attend the study clinic for any further HIV testing to avoid confusion of false positive test results. After the completion and analysis of the whole study with consecutive unblinding of the study Groups, participants will receive an individual unblinding session, indicating the vaccine Group plus false positive HIV test results. In the event of ongoing post-immunization positive ELISA, the volunteers will be invited to attend a specified centre annually until such time as this response has disappeared, and provided with an explanatory identity card in the interim.

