### **17.3 Verification of HIV status of volunteers**

If certification is required at the request of the recruited volunteer/participant, this can be provided by the trial Principal investigator after testing at the trial laboratory. A member of the counseling study team will always give HIV test results at post-test counseling session, unless the volunteer/participant requests otherwise. If a specimen from a volunteer/participant suggests that the volunteer is HIV infected, a second specimen will be collected, retested and the results confirmed. If a volunteer/participant for any reason needs to establish his or her HIV status extended tests will be offered as described above.

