#### **17.5 Social discrimination as result of a post-vaccine response**

The aim is to minimize the possibility of social discrimination in volunteers who develop a positive HIV-ELISA test by providing HIV testing by PCR and certification for volunteers as required. In addition, an identification card stating that the individual has participated in a vaccine trial, with a contact number in case of medical emergency, will be provided. In the unlikely event that a volunteer suffers social discrimination as a result of a post-vaccination response, the clinical investigators will assist the volunteer by asking the volunteers to attend at the study site for counseling and testing whereby the necessary HIV testing including HIV-DNA/PCR will be performed to rule out HIV infection.

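### The Visit 18 card is described as telling every holder, without condition, that standard HIV test results do not mean infection; this is wrong for any infected holder and disagrees with the cards in 17.2 and 17.5

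*Protocol*

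**What the plan says.** Section 8.18, the final visit at week 70, says "All study volunteers will be issued a card signed by the principal investigators". The card is to record participation in an HIV-1 immunization study and to state that "the outcome of standard HIV diagnostic tests do not signify HIV-1 infection". It carries the investigators' names, telephone numbers and addresses. The next sentence offers study-site HIV testing after the study to those who want it.

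Three other places bear on the same matter:

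- Section 17.2 ties a card to an ongoing reactive ELISA after immunization. Those volunteers are invited back yearly "until such time as this response has disappeared, and provided with an explanatory identity card in the interim".
- Section 17.5 describes "an identification card stating that the individual has participated in a vaccine trial, with a contact number in case of medical emergency". Nothing there interprets a test result.
- Section 8.1.1, on consent, is conditional. Volunteers are told "they may develop antibodies that will produce a positive reaction in a routine HIV test, but that provisions have been made to distinguish" a vaccine response from infection.

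On timing, 17.2 says "After the completion and analysis of the whole study with consecutive unblinding of the study Groups, participants will receive an individual unblinding session", so the Visit 18 card comes first. On infections after the trial, 8.1.1 says "HIV infections occurring after the study and observation period will be handled in the regular established HIV clinic in the police force or community".

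**The concern.** The card exists because vaccination can make an uninfected person react in a routine HIV test, and a volunteer should not be labelled infected on that basis. That purpose needs a statement about what a reactive antibody test may mean. The statement described in 8.18 goes further. It covers standard HIV tests in general, it applies to all holders, and it says that their outcome does not signify infection.

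For an uninfected vaccine recipient this is helpful. For an infected holder it is false. A clinician outside the study who relied on it could set aside a true reactive result, and diagnosis and care would be delayed. Section 4 says that, for safety, any HIV vaccine must be presumed capable of increasing transmission until shown otherwise. A signed statement that could lead a reader to discount infection sits badly with that caution.

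**Working it through.** No sample size, power or error rate is involved, and the plan states no figure to reproduce. The check is a comparison of texts, followed by a rough indication of scale.

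**1. Wording of the card, section by section**

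| Section | Who receives it | What it says about tests | Condition or end |
|---|---|---|---|
| 8.18 | All volunteers at Visit 18 | Standard test outcomes do not signify infection | None |
| 17.2 | Those with an ongoing positive ELISA after immunization | Explanatory card, content not given | Until the response disappears |
| 17.5 | Trial participants | Nothing; participation and a contact number | None given |

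These are not one card described three times. Only 8.18 gives an unconditional interpretation of test results.

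**2. For which holders is the 8.18 statement wrong?**

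- *Uninfected vaccine recipients.* The statement serves them as intended.
- *Saline recipients.* There are 3 × 4 = 12 among 120 (section 6.5). They have no vaccine-induced antibody, so the interpretation has no basis for them. It does harm only if they are infected.
- *Volunteers infected during the trial.* HIV infection ends injections but not follow-up (16.1), so they can reach Visit 18 and fall under all volunteers. Their exposure is limited: "If a specimen from a volunteer/participant suggests that the volunteer is HIV infected, a second specimen will be collected, retested and the results confirmed" (17.3), and 17.4 provides referral for care.
- *Volunteers first found infected at Visit 18.* An HIV test is done at that visit, and counselling on negative results follows 2 to 3 weeks later. The text does not make the card wait for the result. A positive result would go through 17.3 and 17.4.
- *Volunteers infected after the study.* This is the main exposed group. They hold the card, study-site testing is optional for them, and their infection is to be handled at police or community clinics.

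**3. Scale**

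The only comparator in the protocol is the earlier DNA and adenovirus-5 vaccine trial in section 4.7.2: 324 enrolled overall, 60 of them in Mbeya, with 3 infections detected after completion. Neither the denominator for the 3 nor the length of post-study observation is given.

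- If all 324 are the denominator: 3/324 = 0.93%, exact 95% CI 0.19% to 2.68%. For 120 holders, 120 × 3/324 = 1.1 (0.2 to 3.2).
- If all 3 came from the 60 in Mbeya: 3/60 = 5.0%, exact 95% CI 1.0% to 13.9%. For 120 holders, 6 (1.3 to 16.7). Nothing in the protocol says that they did.

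A second illustration takes one post-study year with yearly incidence *r*. Expected infections are 120 × *r*, and P(at least one) = 1 − exp(−120*r*).

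| *r* | Source | Expected | P(at least one) |
|---|---|---|---|
| 0.5% | Assumed | 0.6 | 45% |
| 1.0% | Assumed | 1.2 | 70% |
| 1.96% | Police cohort 1994–96 (4.6) | 2.35 | 90% |

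Volunteers here are selected for low risk, so the last row is probably too high. All these figures count infections among card holders. None counts diagnoses missed because of a card.

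**The case against.** The strongest reply is that 8.18 is one clause in a visit description and not the card. The printed text may be more careful. The clause could also be read as saying that a reactive test is not in itself evidence of infection. That reading is possible, but it is not what the words say, and staff who print the card from 8.18 would print the unconditional form.

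The second reply is that the protocol has real safeguards. Section 17.2 advises participants to use the study clinic for later HIV testing. PCR is available for clinical management or on request, and certification is offered in 17.3. The card carries the investigators' telephone numbers. The comprehension test covers both the possibility of infection and the use of other tests to settle status. The later session tells each participant the vaccine group and any false positive results, which largely answers the saline point once it has taken place. All of this stands and lowers the risk. None of it corrects or withdraws the statement on the card.

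The third reply is that the route to harm is inferred, and this is right. Section 8.1.1 says where post-study infections are handled. It does not say where they are first tested, and the advice in 17.2 points towards the study clinic.

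A reader might go further and infer that infections arising in the trial would be missed, or that a known number of former volunteers would be misdiagnosed. The documents support neither. In-trial infections are retested, confirmed and referred, and the figures above measure infections only.

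**Conclusion.** The point holds in a limited form. As described in 8.18, the card makes an unconditional statement that is wrong for any holder who is or becomes infected, in vaccine or placebo groups alike, and that does not match 17.2 or 17.5. It should be corrected. It is a matter of participant safety and of consistency, and it affects no endpoint, estimate or randomization procedure.

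The number affected is unknown and probably few. About 1 infected holder in 120 is a reasonable order of magnitude if the earlier trial's 324 volunteers are the right denominator and if risk and post-study time are similar, neither of which the protocol states. How many of those would meet a reader who relied on the card cannot be estimated. Confidence is moderate, because the printed card is not reproduced and first testing at an outside clinic is an inference.

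**What to change.** Put one identical sentence on every card: a reactive HIV antibody test may be vaccine-induced, it does not by itself show or exclude infection, and the holder should be referred to the study site for PCR-based testing. Describe this same card in 8.18, 17.2 and 17.5. Because the wording is the same for all holders, it reveals nothing about allocation.

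The cost is a small wording amendment with no new visits, samples or assays. It does need ethics committee approval before use, since section 23 requires this for changes that bear on volunteer risk. A conditional sentence is also less categorical in defending an uninfected holder against discrimination, the aim of 17.5. The referral for PCR is what preserves that protection, although the documents do not show that it would protect equally well.

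Two housekeeping items can go into the same amendment but are not part of this point. Weeks 84 and 108 and Visit 19 in 17.2, and weeks 84 and 108 in 20.2, should match the current schedule, which ends at week 70 (Visit 18). The rapid antibody test named in 17.2 and the antigen/antibody ELISA in 12.3.1 should be aligned with the Appendix 7 algorithm. That figure is not shown, so which assay is correct cannot be settled here.

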#### **8.19 Additional visits**

If the volunteer attends or contacts the clinic for any health related changes or event outside the regular study visit schedule the Visit Contact Form (**CRF 2-III**) will indicate this contact as an unscheduled visit. This might include also hospital visits, home visits or the documentation of contacts by phone. A Physical Examination Form (**CRF 3-II**) might be filled as well as the Adverse Event Form (**CRF 6-I**) and Concomitant Medication Form (**CRF 4-I**) if indicated. Unscheduled visits will be numbered based on the previous scheduled visits plus a capital letters ranging from J-Z indicating the sequence of the unscheduled visit (e.g. visit 10I, 10J, etc.).

#### **8.20 Compensation for study participation**

Regular compensations will be made to all volunteers/participants to cover their travel expenses as well as time and inconvenience compensation. For scheduled visits this will

amount to 20,000 TShs (~ 20 USD) for Dar es Salaam and 15,000 TShs (~ 15 USD) for Mbeya, where transport and living costs are lower compared to Dar es Salaam. Unscheduled visits will be compensated with 10,000 TShs in Dar es Salaam and 8,000 TShs in Mbeya. Compensation for unscheduled visits might be rejected in the case of assumed abuse of compensation, which will be up to the study team's decision. During the study volunteers/participants will receive hypoallergenic latex condoms free of charge. If any medication is required as a result of the study, this will also be provided free of charge. Such medication will include painkillers, antipyretics and the like. Treatment and care for minor diseases can be provided by the study and might include painkillers, antipyretics, antibiotics or anti malaria treatment, and iron substitution. In case of hospitalization/or if further care will be required, these will be covered under the medical insurance provided by the National Insurance Corporation of Tanzania Limited; these will be confined to the period of the study.

#### **8.21 Pregnancy reporting and follow up**

For volunteers who become pregnant before completing the vaccine series, no further immunizations will be given. Any discontinuation of the vaccine schedule will be recorded in the Subject Status Form (**CRF 7-I**). A positive UPT test result will be communicated to the volunteer as well as her ineligibility to continue with the vaccination schedule. The volunteer will be followed for all the remaining scheduled visits according to the schedule of procedures for safety evaluation, as well as the maternal outcomes during pregnancy, labor, delivery and post-delivery periods. The infant outcome will also be documented. A Pregnancy Report Form (**CRF 11-I**), which included also information on the maternal and infant outcome will be filled at various time points. According to the study protocol female participants will be required to use an effective contraceptive method until 6 months after the last vaccination, which is the last study visit (Visit 18). Pregnancy test will be performed according to the study flow schedule.

#### **8.22 In the event of study discontinuation**

Study volunteer/participants may withdraw his/her consent to participate in the study at any time without prejudice. Wherever possible, the tests and evaluations listed for the termination visit will be carried out if the volunteer/participant refuses follow-up according to the protocol visit schedule. The study monitor and Data and Safety Monitoring Board (DSMB) will be notified of all study withdrawals within 2 working days for enrolled participants.

Volunteers/participants who withdraw from the study will be replaced only as long as the study is still open for enrolment. No replacement will be allowed when the enrolment is closed. All participants who receive at least one immunization will be included in the safety analysis. If a participant does not complete the immunization schedule secondary to a serious adverse event or toxicity, he or she will continue to be followed according to the protocol visit schedule, and, at a minimum, until the adverse event/toxicity is resolved and/or the cause is identified.

A genuine effort will be made to determine the reason(s) why a volunteer fails to return for the necessary visits. This information will be recorded on the Subject Status Form (**CRF 7-I**).

## 9 IMMUNIZATION

### 9.1 Immunization schedule

While DNA/Placebo immunizations will be performed at weeks 0, 4 and 12, MVA/Placebo will be given at weeks 30 and 46. The immunization schedule is summarized below:

| Study week                                              |    | 0                                                                                                             | 4                                                                                                                 | 12                                                                                                                 | 30                                                              | 46                                                               |
|---------------------------------------------------------|----|---------------------------------------------------------------------------------------------------------------|-------------------------------------------------------------------------------------------------------------------|--------------------------------------------------------------------------------------------------------------------|-----------------------------------------------------------------|------------------------------------------------------------------|
| Injection schedule in days
+/- acceptable time frame |    | 0                                                                                                             | 28 days (+/-3)
post DNA I                                                                                      | 84 days (+/- 7)
post DNA I                                                                                      | 126 days post V8 +14 /-28
days                               | 112 days post V11
+14 /-28 days                               |
| Study Group                                             | N  | 1 st vaccination                                                                                   | 2 nd vaccination                                                                                       | 3 rd vaccination                                                                                        | 4 th vaccination                                     | 5 th vaccination                                      |
| IA                                                      | 36 | DNA I
2 x 0.1ml i.d
(combined plasmid
pools in left and right
arm) total 600µg             | DNA II
2 x 0.1ml i.d
(combined
plasmid pools in
left and right arm)
total 600µg             | DNA III
2 x 0.1ml i.d
(combined
plasmid pools in
left and right arm)
total 600µg             | MVA I
1x 1ml of 10  pfu MVA given
i.m. | MVA II
1x 1ml of 10  pfu MVA
given i.m. |
| IB                                                      | 4  | DNA placebo I
2 x 0.1 ml of saline
given i.d.                                                    | DNA placebo II
2 x 0.1 ml of
saline given i.d.                                                       | DNA placebo III
2 x 0.1 ml of
saline given i.d.                                                       | MVA placebo I
1x 1ml of saline given i.m.             | MVA placebo II
1x 1ml of saline given
i.m.          |
| IIA                                                     | 36 | DNA I
2 x 0.1 ml i.d (1 pool
1 (env) in left arm, 1
pool 2 (gag) in right
arm) total 600µg | DNA II
2 x 0.1ml i.d (1
pool 1 (env) in
left arm, 1 pool 2
(gag) in right
arm) total 600µg  | DNA III
2 x 0.1ml i.d (1
pool 1 (env) in
left arm, 1 pool 2
(gag) in right
arm) total 600µg  | MVA I
1x 1ml of 10  pfu MVA given
i.m. | MVA II
1x 1ml of 10  pfu
given i.m.     |
| IIB                                                     | 4  | DNA placebo I
2 x 0.1ml saline given
i.d.                                                        | DNA placebo II
2 x 0.1ml saline
given i.d.                                                           | DNA placebo III
2 x 0.1ml saline
given i.d.                                                           | MVA placebo I
1x 1ml of saline given i.m              | MVA placebo II
1x 1ml of saline given
i.m           |
| IIIA                                                    | 36 | DNA I
5 x 0.1ml i.d (3 pool 1
(env) in left arm, 2
pool 2 (gag) in right
arm) total 1000µg | DNA II
5 x 0.1ml i.d (3
pool 1 (env) in
left arm, 2 pool 2
(gag) in right
arm) total 1000µg | DNA III
5 x 0.1ml i.d (3
pool 1 (env) in
left arm, 2 pool 2
(gag) in right
arm) total 1000µg | MVA I
1x 1ml of 10  pfu MVA given
i.m. | MVA II
1x 1ml of 10  pfu MVA
given i.m. |
| IIIB                                                    | 4  | DNA placebo I
5 x 0.1 ml saline
given i.d.                                                       | DNA placebo II
5 x 0.1 ml saline
given i.d.                                                          | DNA placebo III
5 x 0.1 ml saline
given i.d.                                                          | MVA placebo I
1x 1ml of saline given i.m              | MVA placebo II
1x 1ml of saline given
i.m           |

